## Abstract

**Background:**

Patients on peritoneal and hemodialysis have accelerated atherosclerosis associated with an increase in cardiovascular morbidity and mortality. The atherosclerosis is associated with increased arterial stiffness, endothelial dysfunction and elevated oxidative stress and inflammation. The aims of this study are to investigate the effects of peritoneal and hemodialysis on arterial stiffness, vascular function, myocardial structure and function, oxidative stress and inflammation in incident patients with end stage kidney disease.

**Methods:**

This is an observational study. Eighty stage five CKD patients will be enrolled and followed for one-year. Primary outcome measures will be changes in 1) arterial stiffness measured by aortic pulse wave velocity, 2) oxidative stress assessed by plasma F_2 _isoprostanes and 3) inflammation measured by plasma pentraxin-3. Secondary outcomes will include additional measures of oxidative stress and inflammation, changes in vascular function assessed using the brachial artery reactivity technique, carotid artery intimal medial thickness, augmentation index and trans thoracic echocardiography to assess left ventricular geometry, and systolic and diastolic function. Patients will undergo these measures at baseline (6–8 weeks prior to starting dialysis therapy), then at six and 12 months after starting dialysis.

**Discussion:**

The results of this study may guide the choice of dialysis modality in the first year of treatment. It may also lead to a larger study prospectively assessing the effect of dialysis modality on cardiovascular morbidity and mortality.

**Trial Registration:**

ACTRN12609000049279

## Background

End stage kidney disease (ESKD) patients undergoing dialysis have a substantially increased risk of cardiovascular morbidity and mortality[1] In 2007, 2311 new patients started dialysis in Australia and New Zealand but, unfortunately, many of these patients will die of cardiovascular disease. (ANZDATA 2007) The decision to undergo either peritoneal or haemodialysis is based on a number of factors. One of the important issues is the potential damage the renal replacement therapy may have on the cardiovascular system. Currently, little is known regarding the differential effects of the dialysis modalities on the cardiovascular system.

Oxidative stress and inflammation are associated with the development of cardiovascular disease in dialysis patients [1,2]. The mechanisms are believed to involve arterial stiffening leading to impaired vascular function [3]. In addition, vascular and myocardial dysfunction are also prominent, increasing the likelihood of cardiovascular disease morbidity and mortality in dialysis patients [4]. A number of studies have documented that peritoneal dialysis is associated with decreased levels of oxidative stress and inflammatory markers compared to haemodialysis [5]. A small number of trials have extended this work to determine associations between oxidative stress and inflammation with vascular or myocardial structure and function with equivocal results [4,6]. To our knowledge, only a few cross sectional studies have compared the effects of different dialysis therapies on surrogate markers of cardiovascular disease [7,8]. As yet, no study has compared the changes in these markers over time in incident dialysis patients.

Measures of arterial stiffness such as aortic pulse wave velocity (PWV) predict morbidity and mortality in patients with kidney disease [9]. Numerous studies have reported that the elevated levels of oxidative stress and inflammation in this population [10-14] are associated with arterial stiffness [15]. Therefore, the purpose of this study is to assess the effect of peritoneal and hemodialysis on arterial stiffness, vascular function, oxidative stress and inflammation and myocardial structure and function. Comparing the effects of dialysis modalities on surrogate cardiovascular markers over time will provide unique important information to assist in the treatment of patients with ESKD. A randomised controlled trial assessing this would be ideal but unethical in Australia as patients are generally given a choice between hemodialysis and peritoneal dialysis.

## Methods

### General Considerations and Study Population

This is a multi-centre, one-year prospective observational study utilising convenience sampling. Eighty stage five CKD patients, not yet on dialysis, will be enrolled. They will commence either haemodialysis or peritoneal dialysis according to clinical need and personal preference after undertaking pre-dialysis education. They will be followed for one year after the commencement of their treatment modality. Although this design may be a limitation it is the only ethical one for our aims.

### Location

Patients will be recruited from the Royal Brisbane and Women's Hospital, Brisbane, and the Launceston General Hospital and Satellite Renal Unit Burnie which service populations of approximately 1.2 million and 250,000 respectively.

### Inclusion Criteria

Patients must satisfy the following criteria prior to entering the study: 1) age > 18 and < 85 years, 2) an estimated glomerular filtration rate (eGFR) of < 15 mL/min/1.73 m^2^, 3) undertaken pre-dialysis education program, 4) provide written informed consent.

### Exclusion Criteria

Failure to gain consent or inability to tolerate glyceryl trinitrate (GTN).

### Allocation

The trial is utilising a sample of convenience recruiting participants whom will likely commence either haemodialysis or peritoneal dialysis within three-six months. Approximately six-eight weeks prior to commencing their treatment modality, all eligible patients will undergo baseline measurements of vascular and myocardial structure and function and blood will be collected for the oxidative stress and inflammatory measures. They will then undergo the same measurements at six and 12 months after commencing their chosen treatment.

### Selection and Recruitment of Patients

The nephrologists, trial co-ordinators and research assistants will be responsible for the selection of all eligible patients to be approached. Medical records will be screened prior to attendance at pre-dialysis education clinics. At this stage patient preference for dialysis treatment modality is discussed. After explanation of the study, the subject will be provided with a patient information sheet and informed consent form. The subject will then be asked to take this away with them and arrangements will be made to follow up via a telephone call. If the subject agrees to participate, they will sign the consent form.

### Blood Sampling

A trained phlebotomist will take 40 millilitres of blood during visits to their hospital pathology laboratory or taken on dialysis once this has started.

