#### Oxidative stress and inflammation

The primary outcome measure for oxidative stress will plasma F_2 _isoprostane measured using gas chromatography mass spectrometry [17] and for inflammation, pentraxin 3 using an ELISA assay [18].

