### Visit One (baseline data)

The study flow is summarized in Figure 1 and the study evaluations are outlined in Table 1. After obtaining informed consent, patients will be contacted by telephone by the trial coordinator at which a date and time is agreed for the subject to attend an appointment for baseline trial measures. A letter of confirmation of this appointment and a pathology request form will be posted (if consent formed is signed). Patients will be asked to attend the pathology laboratory at least seven days before their first trial visit to have a fasting blood sample collected. At the first trial visit, if not already done so, the consent form will be signed and additional data will be obtained from the medical records (medical history, medications) and measures of height, weight and blood pressure will be recorded. PWV, PWA, CIMT, TTE and BAR measures will then be made. At the completion of baseline data acquisition, the trial coordinator provides the subject with a pathology request form, for which blood samples are taken within the first week of visit one. The subject will be provided with two questionnaires (SF 36 and items from Active Australia) and a four-day diet diary for completion to take home. The subject is supplied with a self-addressed express post envelope. Subjects are asked to complete and post these within the following two weeks. Data obtained are transcribed onto case record forms for entry into a specifically designed trial database. Subjects are then reminded that they will be contacted by telephone in approximately five months to confirm an appointment date and time for visit two.

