### Visits Two and Three

These visits occur at six months and one year after commencement of dialysis. An envelope containing a letter confirming appointment, pathology request forms, four-day diet diary, SF 36 and physical activity surveys will be mailed to patients. They will be asked to complete surveys and the diet diary and to attend the pathology laboratory seven days prior to visits. At these visits, data acquisition from measures and tests described above will be performed again. Patients will be examined on a non-haemodialysis day for hemodialysis patients and during the non-dwell phase period for peritoneal dialysis patients.

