#### Statistical analysis

All baseline continuous variables between groups will be compared using general linear modelling, whilst categorical variables will be compared using exact logistic regression. The rates of change will be estimated for each patient separately by linear regression. general linear modeling, will be used to compare the mean rate of change in primary outcome measures between groups, unadjusted and adjusted for actual and potential confounding variables. Mean differences, 95% confidence intervals and P-values will be corrected for repeated measures, and P-values corrected for multiple comparisons by the Holm method. All analyses will be performed using Stata/IC 10.1 for Windows (StataCorp LP, College Station, Tx).

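### Follow-up blood may be drawn on dialysis under one section but only at the laboratory under another, which allows a modality-dependent sampling difference in two of the three primary outcomes

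*Protocol article*

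**What the plan says.** All references are to the protocol article.

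- **Blood Sampling:** blood is taken "during visits to their hospital pathology laboratory or taken on dialysis once this has started". Nothing is said about when in a session an on-dialysis sample would be drawn.
- **Visits Two and Three:** patients are asked "to attend the pathology laboratory seven days prior to visits". No on-dialysis alternative is given. A later sentence adds: "Patients will be examined on a non-haemodialysis day for hemodialysis patients and during the non-dwell phase period for peritoneal dialysis patients".
- **Visit One (baseline data):** patients attend the laboratory "at least seven days before their first trial visit to have a fasting blood sample collected". After the visit they receive a further request form, "for which blood samples are taken within the first week of visit one". Fasting is stated only for the first of these samples, and the section does not say which one supplies the primary markers.
- **Allocation:** baseline measures and blood come about six to eight weeks before dialysis starts.
- **Oxidative stress and inflammation** (primary outcomes): plasma F2-isoprostane for oxidative stress, "and for inflammation, pentraxin 3 using an ELISA assay". The third primary outcome, aortic pulse wave velocity, does not depend on blood.
- **Statistical analysis:** "The rates of change will be estimated for each patient separately by linear regression". Mean rates are then compared between the modalities, unadjusted and adjusted for confounders.

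**The concern.** Two sections govern the same 6- and 12-month samples and give different rules. This matters because the samples feed two of the three primary outcomes, and the primary contrast is change over time compared between modalities.

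Baseline blood cannot be drawn on dialysis; follow-up blood can. If some or all haemodialysis patients are sampled at a session while peritoneal dialysis patients keep going to the laboratory, the sampling condition changes with time in one group and not in the other. An acute effect of the session on either marker would then be read as a longer-term effect of modality.

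The protocol recognises this kind of problem for the examination at the visit, where it fixes a condition for each modality. It does not extend that standardisation to blood.

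**Working it through.** **1. The passages side by side**

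| Sample | Rule | Source |
|---|---|---|
| Baseline | Laboratory, before dialysis; fasting stated for one of two draws | Visit One; Allocation |
| 6 and 12 months | Laboratory, seven days before the visit | Visits Two and Three |
| Any time after dialysis starts | Laboratory or on dialysis | Blood Sampling |

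The second and third rows cover the same samples and disagree. The non-haemodialysis-day and non-dwell rule is worded for the examination, while blood is scheduled a week earlier. The direct conflict is therefore with the laboratory instruction.

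**2. How a shift would reach the primary contrast**

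The plan states no figure on this point, so there is none to reproduce. For a least-squares slope through three visits, the weight of the visit at time t_i is w_i = (t_i − t̄) / Σ(t_j − t̄)².

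- Times 0, 0.5 and 1 year: t̄ = 0.5 and Σ = 0.25 + 0 + 0.25 = 0.5, so the weights are −1, 0 and +1. A shift at both follow-ups passes through at 0 + 1 = 1.00.
- Baseline at −7 weeks (midpoint of six to eight weeks; −7/52 = −0.135 year): the weights are −0.912, 0.069 and 0.843. A shift at both follow-ups passes through at 0.069 + 0.843 = 0.91.

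If a fraction f of haemodialysis patients have both follow-up samples shifted by δ, and no peritoneal dialysis patients do, the bias in the difference of mean annual rates is f × δ × (0.91 to 1.00).

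**3. Scale, with assumed shifts**

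Inputs from Sample Size Estimates: pentraxin-3 0.75 ± 0.3; a 10% decrease taken as clinically significant, so 0.10 × 0.75 = 0.075; 37 haemodialysis and 23 peritoneal dialysis completers. The shifts are assumptions. The SD of change is not given, so the SD of 0.3 stands in for it:

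SE = 0.3 × √(1/23 + 1/37) = 0.080.

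Two-sided type I error at nominal 0.05, normal approximation: 1 − Φ(1.96 − b/SE) + Φ(−1.96 − b/SE), where b is the bias with pass-through 1.00.

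| Assumed shift | Share of HD patients | Bias | Bias ÷ 0.075 | Type I error |
|---|---|---|---|---|
| 0% | any | 0 | 0 | 0.050 |
| 5% | all | 0.0375 | 0.5 | 0.076 |
| 10% | a quarter | 0.019 | 0.25 | 0.056 |
| 10% | half | 0.0375 | 0.5 | 0.076 |
| 10% | all | 0.075 | 1 | 0.156 |
| 20% | all | 0.15 | 2 | 0.469 |

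With pass-through 0.91, the 10% shift in all patients gives 0.91 × 0.075 = 0.068. A downward shift gives the same sizes with the opposite sign.

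**The case against.** The strongest reply is that the text only permits on-dialysis sampling. It does not require it, and it does not place the draw during the session; a sample taken before the circuit runs could be equivalent to a laboratory sample. The documents report no effect of a session on either marker, so the shifts above are assumptions and their ratio to the target follows by construction. Restriction to haemodialysis is also an inference, since Blood Sampling does not limit the phrase to one modality. All of this stands.

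Fasting at follow-up may carry over from baseline, because Visits Two and Three says the measures and tests already described are repeated. An article may also leave draw timing to the full protocol. It is therefore not shown that follow-up samples would be non-fasting.

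The analysis plans adjustment for confounders. If only some haemodialysis samples are drawn on dialysis, the draw condition varies within that group and its effect could be estimated, provided it is recorded. That also stands. Only if every haemodialysis follow-up sample were drawn on dialysis could adjustment not separate session from modality.

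The two baseline timings apply to all patients before dialysis and create no difference between modalities. They are a separate, smaller ambiguity.

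None of this removes the conflict between the two sections. Leaving detail to a fuller document does not explain two different stated rules for the same samples.

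**Conclusion.** The concern holds in a limited form. Blood Sampling and Visits Two and Three conflict on where follow-up blood is drawn. As written, the protocol allows a sampling difference in F2-isoprostanes and pentraxin-3 that may depend on both modality and time, and any session effect would enter the primary comparison of rates of change. This rests on the natural reading that an on-dialysis draw means a haemodialysis session.

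The size is unknown. An assumed 10% pentraxin-3 shift in all haemodialysis follow-up samples would give a bias of about 0.07 to 0.075, close to the plan's whole target. It would be proportionately less if fewer samples were affected, and zero if on-dialysis and laboratory samples are equivalent.

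A reader might infer more, and the documents do not support it:

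- That an artefact is certain, or that it favours the peritoneal dialysis hypothesis. Neither its existence nor its direction is given.
- That on-dialysis sampling breaks the non-haemodialysis-day rule. That rule is worded for the examination, so the tension is one of intent.
- That sampling condition and modality are fully confounded. This needs every haemodialysis follow-up sample to be drawn on dialysis, and the text offers that only as an alternative.

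**What to change.** 1. Reconcile Blood Sampling with Visits Two and Three into one research blood-sampling condition for both groups at all visits: at the laboratory, off dialysis, in the same fasting state as the baseline sample. For the primary-marker samples, delete the on-dialysis alternative.
2. In Visit One, state which of the two baseline samples supplies F2-isoprostanes and pentraxin-3.
3. Record draw date, fasting status and time since last dialysis for every sample.
4. Keep any sample still drawn during a session in the primary analysis, and examine its influence in a sensitivity analysis. Excluding such samples from the primary analysis would probably remove data from the haemodialysis group only, creating missingness that depends on modality.

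The cost is protocol wording and a few record fields. Some haemodialysis patients will need a laboratory draw separate from their session, but Visits Two and Three already schedules it. The change should be made before follow-up sampling: if draw conditions are not recorded, the problem cannot be repaired afterwards.

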### Ethical Considerations

The Tasmanian Statewide Scientific and Ethics Committee has approved the study. The Ethics Committee will be provided with annual reports of the trial progress and will promptly receive all adverse event reports.

### Primary Objectives and Primary Outcome Measures

The primary objectives are to assess the effects of dialysis modality on arterial stiffness and oxidative stress and inflammation. The hypothesis is that peritoneal dialysis will significantly improve the rates of change in these measures compared with hemodialysis. The primary outcome measures are outlined below.

#### Arterial stiffness

The primary outcome for arterial stiffness will be aortic PWV. Carotid to femoral PWV will be derived by electrocardiography-gated sequential applanation tonometry (SPT-301 Mikro-Tip, Millar Instruments, Houston, Texas) using the foot-to-foot method (SphymoCor™ 7.01 AtCor, Sydney, Australia) [16]. Testing is performed in a temperature-controlled room and after 5–10 minutes rest with the subject in the supine position prior to the first measure. Two measures will be averaged for the estimation of aortic PWV.

#### Oxidative stress and inflammation

The primary outcome measure for oxidative stress will plasma F_2 _isoprostane measured using gas chromatography mass spectrometry [17] and for inflammation, pentraxin 3 using an ELISA assay [18].

### Secondary Objectives and Secondary Outcome Measures

Secondary objectives are to assess the effects of dialysis modality on vascular structure and function, myocardial structure and function and additional measures of arterial stiffness, oxidative stress and inflammation.

#### Vascular Structure and Function

Carotid Intimal Media Thickness (CIMT) will be used to measure structural alterations of the posterior wall of both the left and right common carotid arteries. CIMT refers to the combined thickness of the intimal and medial layers of the carotid arterial wall [19]. This corresponds to the inner and outer echogenic lines seen on the B-mode ultrasound image [20]. The CMIT will be assessed using a 12 MHz linear array transducer and ultrasound scanner (Vivid i, GE Healthcare, USA). Images will be acquired from the anterior, posterior and lateral planes of the right and left common carotid arteries. The thickness will be measured one to two centimetres proximal to the bifurcation and during cardiac diastole from the far wall only as there are technical and acoustic difficulties encountered when measuring the near wall thickness [20]. For the purpose of this study, the average of these six recordings will be used. CIMT assessment will be performed in the plaque-free arterial wall (an atherosclerotic plaque being defined as an echo-structure protruding into the vascular lumen and a thickness greater by at least 50% than neighbouring sites [21].

Brachial artery reactivity (BAR) will be measured to assess vascular function. A 12 MHz linear array transducer and ultrasound scanner (Vivid i, GE Healthcare, USA) will be used to record the dilator response of the brachial artery to increased blood flow generated during reactive hyperaemia of the downstream forearm. The measures will be performed on the non-fistula arm (if a fistula is present). A blood pressure cuff is placed on the upper aspect for the lower forearm. The brachial artery will be scanned in the longitudinal plane, acquiring a baseline image about five cm above the antecubital fossa. The transducer is left in this scanning position. The cuff is then inflated to 220 mmHg for four minutes. Following cuff deflation, images will be acquired at five and 10 seconds then at 10-second intervals up to 120 seconds. Following a 15-minute rest, this process is then repeated. The 15-minute interval allows the artery to return to its baseline state. The last phase of the BAR test involves the administration of sublingual GTN. Following a final 15-minute interval, a baseline image is acquired and then 300 μg of sublingual GTN will be administered. After three minutes, images of the brachial artery will be obtained as described above. All images will be stored for later offline analysis and archiving. The truest diameter of the brachial artery is indicated by the "double line sign", which is the crisp intima-media and media-adventitia boundaries on the near and far walls [22]. For all measures, the average of three diameter measurements made along the artery, from the trailing edge of intima-media to the leading edge of the media-adventitia, as described by Aeschlimann et al [22], will be used. BAR will be expressed as maximal dilatation (mm), and expressed as a percentage change from baseline. The area under the diameter/time curve (AUC) will also be used to determine temporal changes using analytical imaging software (Imaging Research, St. Catherine's, Canada) and confirming with trapezoidal integration in Microsoft Excel (Seattle, WA, USA) as we have done previously [23]. These will then be compared with the dilatation in response to the administration of GTN. This provides a ratio of endothelial dependant and independent vascular function.

